### 2.6. Randomization, allocation, and blinding

Randomization and allocation will start on day 2 or 3 of the previous menstrual cycle before IVF. Eligible women will be stratified by AFC (<5 or ≥5) and randomized within the 2 strata. All participants will be randomly assigned to either the EZTG group or the placebo group in a 1:1 ratio. Randomization will be completed by software (R 4.0.0, R Foundation for Statistical Computing, Vienna, Austria), and different-sized block groups of 2, 4, 6 will be applied. Random number tables will be provided by statistical professionals not involved in the rest of the study and the number will be sealed into brown envelopes. Then the group allocation will be accomplished by opening envelopes sequentially in the order in which patients were recruited.

A double-blind study design will be applied to enhance the quality of the study evidence. Both medications (EZTG granules and placebo) will be prepared in a manner that they will appear similar in appearance, flavor, and smell. Clinicians and patients will not be able to distinguish the difference between groups. The outcome assessment and data analysis will also be conducted in blinding. When the clinical trial is over, the final blind-break process is performed by authorized researchers.

### 2.7. Interventions

#### 2.7.1. Therapeutic drug preparation and administration.

The experimental drug EZTG will be in the form of granules, obtained from the original EZTG formula mixture after decocting, concentrating, and drying. The granules are produced by the Drug Manufacturing Unit of the Affiliated Hospital of Shandong University of Traditional Chinese Medicine and packaged as 3 g/bag, batch number 01-FZ032-03. Genuine medicinal materials are used in all kinds of traditional Chinese herbs including: Cuscuta chinensis (Tu Si Zi), Ligustrum lucidum (Nv Zhen Zi), Herba Ecliptae (Mo Han Lian), Fructus Lycii (Gou Qi Zi), Angelica sinensis (Dang Gui), Radix Rehmanniae Preparata (Shu Di Huang), Ligusticum wallichii (Chuan Xiong), Paeonia lactiflora (Bai Shao), Rhizoma cyperi (Xiang Fu), Radix Glycyrrhizae Preparata (Zhi Gan Cao). All the dosage is within the safe limit specified in the Chinese Pharmacopoeia.

Method of administration: 3 bags each time, 3 times a day, orally, administered after being dissolved in warm water. Participants were required to take the EZTG from day 2 or 3 of the previous cycle that precedes the IVF cycle to the day of the trigger. The crude herbal dosage and pharmacological efficacy of the herbs in EZTG granules are summarized in Table 2. Figure 2 shows the picture of Chinese herbal medicine in EZTG.

**Table 2 T2:** Ingredients and effects of Chinese herbal medicine in the EZTG granules.

Components	Crude herbal dosage (g/d)	Related pharmacological effects
Tusizi (Cuscuta chinensis)	9	Anti-inflammation, anti-aging, relieving pain, or aphrodisiac.
Nvzhenzi (Ligustrum lucidum)	9	Abrogation of cell apoptosis and cell senescence; hepatoprotective effect, anticancer activity, antioxidant activity, and immunomodulating effect.
Mohanlian (Herba Ecliptae)	9	Promoting osteoblastic differentiation, and thus treating osteoporosis.
Gouqizi (Fructus Lycii)	9	Oxidative stress alleviation, antiaging, and senescence delay.
Danggui (Angelica sinensis)	6	Hematopoietic activity, promoting immunity, antitumor, anti-inflammation, antioxidant, anti-aging, anti-virus, and liver protection.
Shudihuang (Radix Rehmanniaen Preparata)	9	Improvement of energy metabolism dysfunction, relegation of the peripheral circulation system, and relieving oxidative damage in the body.
Chuanxiong (Ligusticum wallichii)	6	Regulation of the circulatory system, anti-inflammation, and abrogation of cell apoptosis.
Baishao (Paeonia lactiflora)	6	Activation of ovarian angiogenesis and follicular development.
Xiangfu (Rhizoma cyperi)	6	Anti-depression, hypoglycemic effect, anti-oxidation, anti-inflammation, anti-tumor and antibacterial effect.
Zhigancao (Radix Glycyrrhizae Preparata)	10	Regulation of lipid and glucose metabolisms and anti-cancer, as well as immunomodulatory and hepatoprotective effects.

EZTG = Erzhi Tiangui.

**Figure 2. F2:**
[figure not shown]
The picture of Chinese herbal medicine in EZTG. EZTG = Erzhi Tiangui.

#### 2.7.2. Placebo preparation and administration.

The placebo granules, which were mainly composed of dextrin and caramel, were made in a similar color and shape to EZTG. The placebo granules have no active ingredients and therefore have no efficacy. The method of administration was the same as the EZTG. Both the EZTG and placebo production will be consistent with the Chinese Medicine Standards of the State Food and Drug Administration.

#### 2.7.3. COS and oocytes retrieval.

Participants will be assessed again for eligibility on day 2 or 3 of the IVF cycle. The participants will also receive hormonal and ultrasound assessments to ensure the feasibility of COS.

Eligible participants will be administrated COS with a Gonadotrophin-releasing hormone antagonist protocol on day 2 or 3 of the menstrual cycle and given recombinant follicle stimulating hormone (Gonal-F, Merck Serono, Switzerland). The starting dose of rFSH will be in a range between 150–225 IU/day, based on the individual baseline characteristics. The COS process will be individualized, and the follow-up dose of rFSH will be adjusted according to the ovarian response during COS every 2 or 3 days. On day 5 or 6 of the ovarian stimulation, gonadotrophin releasing hormone-antagonist (cetrorelix acetate, Cetrotide; Merck Serono, Germany) will be initiated. When more than 2 follicles are at least 18 mm, 250 mg of recombinant human chorionic gonadotrophin will be administered to trigger the final follicular maturation. After 35 to 37 hours, transvaginal ultrasound-guided aspiration is performed. Intracytoplasmic sperm injection will only be performed in cases of severe male factors of infertility.

#### 2.7.4. Embryo transfer and luteal phase support (LPS).

All patients received cleavage-stage embryo transfer on day 3 after oocyte retrieval, or blastocyst transfer on day 5, except for the following cases: uterine or endometrial abnormalities, such as endometriosis, uterine fibroids, endometrial polyps or intrauterine adhesions; serum *P* > 1.5 ng/mL on the trigger day. No more than 2 embryos will be transferred per transfer. Among participants receiving embryo transfer, LPS will be administrated until 10 weeks of gestation, with an intramuscular P4 injection of 40 mg per day or vaginal P4 (8% Crinone, Merck Serono, Switzerland) 90 mg per day, plus dydrogesterone tablet (Duphaston, Abbott, Hoofddorp, Netherlands) 30 mg per day. The LPS will be discontinued if the pregnancy failure has been confirmed by the serum pregnancy test or ultrasound assessment.

### 2.8. Outcomes

#### 2.8.1. Efficacy outcomes.

The primary outcome is the number of oocytes retrieved per COS cycle.

The following secondary outcomes will also be evaluated as secondary outcomes:

Symptom rating scores of kidney qi-yin deficiency syndrome after treatment (The symptom rating scales is shown in Table 3).Difference in rating scores of kidney qi-yin deficiency syndrome before and after treatment.Average daily dose of gonadotropin per COS cycle.Total gonadotropin dose and duration of ovarian stimulation per COS cycle.Cycle cancelation rate per COS cycle. Cycle cancelation is defined as a cycle canceled before obtaining at least 1 viable embryo for any reason.Good quality embryos rate per embryo. A good quality embryo is defined as an embryo that is graded as 6-cell grade 2 (6CII) or better or blastocyst.Embryo implantation rate per embryo, defined as the number of gestation sacs detected divided by the number of embryos transferred.Clinical pregnancy rate per patient, defined as the number of women with identified clinical pregnancies divided by the number of patients randomized to a specific group. Clinical pregnancy is confirmed when 1 or more gestational sacs are detected on transvaginal ultrasound assessment.Early miscarriage rate per patient, defined as the percentage of participants with loss of a diagnosed clinical pregnancy before 12 weeks gestation to the total patients randomized.CLBR per patient, defined as the proportion of deliveries with at least 1 live birth per started cycle or oocyte aspiration, including all fresh and/or frozen embryo transfers until 1 delivery with a live birth or until all embryos were used (within 1 year after randomization).

**Table 3 T3:** Symptom rating scales of kidney qi-yin deficiency syndrome.

Symptoms	Characteristics and severity of the symptoms	Score
The color and quality of the menstruation	The color of the blood is dark red and the quality is thin and watery	5
	The color of the blood is dark red or the quality is thin and watery	3
	Normal color and quality	0
The waist and knees are sour and powerless, or pain in the heels	Severe discomfort that interferes with daily life	6
	Moderate discomfort	4
	Mild discomfort	2
	No obvious discomfort	0
Dizziness and tinnitus	Severe, occurs constantly and interferes with daily life	6
	Moderate, occurs frequently	4
	Mild, occurs occasionally	2
	Not obvious	0
Mental exhaustion	Severe, occurs constantly and interferes with daily life	6
	Moderate, occurs frequently	4
	Mild, occurs occasionally	2
	Not obvious	0
Low sexual desire	Low sexual desire, no intercourse	6
	Low sexual desire, intercourse once a month	4
	Low sexual desire, intercourse once a week	2
	Normal sexual desire	0
Less vaginal discharge, and loss of armpit or pubic hair	Less vaginal discharge and loss of armpit or pubic hair	6
	Less vaginal discharge or loss of armpit or pubic hair	4
	Thin armpit or pubic hair	2
	Normal	0

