#### 2.4.3. Inclusion criteria.

Women aged ≥35 years, eligible for IVF or Intracytoplasmic sperm injection treatment.Women who meet the diagnostic criteria for POR.Women who meet the diagnostic criteria for kidney qi-yin deficiency syndrome.

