### 2.9. Statistical analysis

#### 2.9.1. Sample size calculation.

##### 2.9.1.1. Sample size calculation

Sample size calculations referred to previous studies, and the clinical outcomes of aged women with POR from the electronic database in our reproductive center.^[9,23]^ The study was designed to detect a difference between groups in terms of 1 additional retrieved oocyte after the hCG trigger with a standard deviation of 3 retrieved oocytes. The power is set at 90%, along with a 2-sided 5% type I error rate. To account for a 20% dropout rate, the sample size of 480 was determined using PASS 15.0 (NCSS, LLC, Kaysville, Utah), in which 240 participants were in each group.

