#### 2.9.2. Planned data analysis.

Intention-to-treat (ITT) analysis will be used for baseline comparisons and the assessment of the effect of EZTG on the total number of retrieved oocytes per COS cycle, as well as other secondary outcomes. T-test, Wilcoxon rank-sum test, or chi-square test will be used to test for differences. The results will be given as mean (standard deviation), median (interquartile range), or frequency (percentage) according to the type and distribution of the variables. A 2-sided *P* < .05 is considered statistically significant with a confidence interval of 95%. Per protocol analysis will be conducted as a sensitivity analysis, including those patients who completed their randomized treatment. If the ITT results conflict with the per protocol results, we will interpret the study results according to the outcome of the ITT analysis.

In addition, a subgroup analysis will be performed according to AFC strata (<5 or ≥5) using a similar approach to the primary analysis. Multiple imputations will be used to process missing values in the data of this study. All statistical work will be performed on SPSS version 26.0 software (IBM Corporation, Armonk, NY).

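### One symptom scale yields two separately tested secondary outcomes, neither named as leading and neither adjusted for the baseline score as a covariate

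*Protocol article*

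**What the plan says.** Section 2.8.1 of the protocol article gives two secondary outcomes from the rating scale in Table 3: "Symptom rating scores of kidney qi-yin deficiency syndrome after treatment" and "Difference in rating scores of kidney qi-yin deficiency syndrome before and after treatment". The text does not say which is the main symptom result.

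Section 2.9.2 applies one analysis paragraph to the primary outcome "as well as other secondary outcomes". Its methods are stated as: "T-test, Wilcoxon rank-sum test, or chi-square test will be used to test for differences". A two-sided P below .05 "is considered statistically significant with a confidence interval of 95" percent. None of the named tests takes a covariate. The section mentions baseline only for comparing the groups at entry, and the other analyses it names are per protocol, AFC subgroups and multiple imputation.

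Section 2.4.3 admits "Women who meet the diagnostic criteria for kidney qi-yin deficiency syndrome", so the syndrome is assessed at entry. The planned before-after difference needs a baseline score from every woman in any case.

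**The concern.** The two outcomes ask the same question of one measurement but treat the baseline score differently. The raw post-treatment score ignores it. The difference subtracts it in full. Where the true regression of post-treatment on baseline score has a slope between 0 and 1, the first under-corrects for a chance imbalance and the second over-corrects.

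Three things follow:
- the two results can disagree, and the plan has no rule for which one answers the question;
- the trial has two unadjusted chances at a significant symptom result;
- neither analysis makes the best use of a baseline score that is already being collected.

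The Discussion (section 3) treats women's perception of their symptoms as central in TCM theory and lists these scores among the improvements over the pilot study. A measure given that weight should lead to one prespecified answer.

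**Working it through.** **The plan's own figure.** The only sample-size figure concerns the primary outcome (section 2.9.1.1: difference 1 oocyte, SD 3, 20% dropout; "The power is set at 90" percent, "along with a 2-sided 5% type I error rate"). The normal formula gives 190 per arm; 190/0.80 rounds up to 238, or 476 in total. The t-based version gives 191, then 239 per arm, or 478. The stated 480 reproduces and is not in dispute. For the symptom score the article gives no SD, effect size or baseline-to-follow-up correlation, so these are assumptions below.

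**The scale.** Table 3 has one item with a maximum of 5 and five with a maximum of 6: 5 + 5 × 6 = 35. Section 2.4.2 makes two symptoms mandatory, and on Table 3 these score at least 3 and at least 2. If the items are summed, the lowest eligible total is about 3 + 2 = 5. The required third symptom may be the pulse sign, which is not on the scale, so the other four items can all be 0.

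**Direction under chance imbalance.** Let b be the slope of post-treatment on baseline score. Suppose one arm starts d points higher and there is no treatment effect.
- Expected difference in raw post-treatment score: b·d
- Expected difference in change: (b − 1)·d

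For 0 < b < 1 these have opposite signs.

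**Precision.** Set the post-treatment variance to 1, the baseline SD to k and the correlation to r, so b = r/k.
- Raw post-treatment score: 1
- Change: 1 + k² − 2rk, which is 2(1 − r) when k = 1
- Baseline-adjusted (ANCOVA): 1 − r²

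| | r = 0.3 | r = 0.5 | r = 0.7 |
|---|---|---|---|
| Raw score | 1.00 | 1.00 | 1.00 |
| Change, k = 1 | 1.40 | 1.00 | 0.60 |
| Change, k = 0.7 | 1.07 | 0.79 | 0.51 |
| Adjusted, any k | 0.91 | 0.75 | 0.51 |

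With k = 1, adjustment beats both outcomes for every r strictly between 0 and 1. With k = 0.7 and r = 0.7 the slope is 0.7/0.7 = 1, and the change score ties with ANCOVA at 0.51.

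**Two chances at significance.** With no effect, the two test statistics correlate at (1 − rk)/√(1 + k² − 2rk). The bivariate normal probability that at least one exceeds 1.96 in absolute value is:
- k = 1: correlations 0.59 / 0.50 / 0.39, probability 8.8% / 9.1% / 9.4%
- k = 0.7: correlations 0.76 / 0.73 / 0.71, probability 8.0% / 8.2% / 8.3%

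**How often the P values would split.** Take 192 per arm (240 less 20%), k = 1 and an assumed true effect of 0.3 SD. In 200,000 simulated trials, exactly one of the two tests was significant in about 25% / 20% / 17% at r = 0.3 / 0.5 / 0.7. Power for raw / change / adjusted was 83.6 / 70.0 / 86.9% at r = 0.3, 83.6 / 83.6 / 92.4% at r = 0.5 and 83.6 / 96.7 / 98.4% at r = 0.7.

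**The case against.** Several points against the concern stand.

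- A reader might infer that neither outcome uses the baseline score. That is not so: the difference subtracts it. What is missing is adjustment for it as a covariate.
- A reader might also infer that women with low scores start at the floor. The documents do not support this. Single items can be at 0, but the lowest eligible total is about 5 of 35, which is near the floor rather than at it.
- The variance figures need equal SDs before and after as well as a correlation, and entry on symptoms may narrow the baseline spread. At a baseline SD 0.7 times the post-treatment SD the advantage over the change score shrinks, and at r = 0.7 it disappears.
- Randomization keeps both estimates unbiased. The standard error of a chance baseline difference is √(2/n) in SD units, about 0.10 at 192 per arm and 0.09 at 240, so large imbalances are unlikely. A split between P values is not by itself a conflict in the direction of effect.
- These are two of about ten secondary outcomes with no confirmatory claim attached, and reporting both a final score and a change is common and valid.

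It can also be argued that covariate adjustment belongs in an analysis plan that is not shown. That carries less weight here. Section 2.9.2 is not silent: it names the tests for the secondary outcomes and none of them adjusts. Section 2.8.1 itself sets up the pair without an order.

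**Conclusion.** The point holds as a matter of precision and clarity for a secondary outcome. Two outcomes from one scale are each tested unadjusted at P < .05 with no lead.

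Neither is more precise than a baseline-adjusted comparison. Relative to ANCOVA, the raw score carries 1/0.91 = 1.10, 1/0.75 = 1.33 or 1/0.51 = 1.96 times the variance at r = 0.3, 0.5 or 0.7, whatever the SD ratio. The penalty for the change score depends on that ratio and can be nil. The chance of at least one false-positive symptom result is about 8–9% rather than 5%. The opposite pull of a chance imbalance requires a slope between 0 and 1, which is plausible but not established by the documents.

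A reader might infer that the symptom results would be biased or that the trial's main conclusion is at risk. Neither follows: both estimates are unbiased, and the primary outcome and the 480 are unaffected.

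**What to change.** In sections 2.8.1 and 2.9.2, name one lead symptom analysis: the post-treatment score compared between arms by ANCOVA, with baseline score and AFC stratum (<5 or ≥5, already the randomization stratum) as covariates. Add a rank-based ANCOVA as a sensitivity analysis in case the score is skewed. Keep the raw post-treatment score and the before-after difference as descriptive results, without separate significance claims.

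No listed outcome has to be deleted, which limits any question of outcome switching. The trial is registered and enrolment was scheduled from May 2023 (section 2.1), so the change should be made as a short, dated amendment before unblinding. It needs no extra visit or data, because the baseline score is already required for the difference, and SPSS fits ANCOVA.

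### Good-quality-embryo and implantation rates are defined per embryo, but none of the tests named allows for embryos clustering within the randomised woman

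*Protocol article*

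**What the plan says.** Section 2.6 makes the woman the unit of randomisation: "All participants will be randomly assigned to either the EZTG group or the placebo group in a 1:1 ratio".

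Section 2.8.1 makes the embryo the unit of two secondary outcomes. One is the "Good quality embryos rate per embryo". The other is the "Embryo implantation rate per embryo, defined as the number of gestation sacs detected divided by the number of embryos transferred".

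A woman can contribute more than one embryo to either. Section 2.7.4 sets a ceiling per transfer: "No more than 2 embryos will be transferred per transfer". Repeated transfers are foreseen, "including all fresh and/or frozen embryo transfers until 1 delivery with a live birth or until all embryos were used", although Section 2.8.1 says this only when it defines the cumulative live birth rate.

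Section 2.9.2 applies ITT to the primary and secondary outcomes and gives one list of tests for all of them: "T-test, Wilcoxon rank-sum test, or chi-square test will be used to test for differences". On presentation it says: "The results will be given as mean (standard deviation), median (interquartile range), or frequency (percentage) according to the type and distribution of the variables". A two-sided P below .05 "is considered statistically significant with a confidence interval of 95"%. No GEE, mixed model, robust variance or per-woman summary is mentioned.

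**The concern.** The stated unit and the stated tests do not fit each other. Embryos from one woman share the same parents, cycle and uterus, so their outcomes are expected to be positively correlated. All three listed tests assume independent observations. Applied to pooled embryos, they credit the trial with more information than it has, which makes P values too small and intervals too narrow.

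A second, separate matter concerns the denominators. Embryos obtained and embryos transferred both arise after randomisation and exist only for women who reach that stage. The treatment is intended to raise oocyte yield and so may change them. A per-embryo rate is therefore not a comparison of all randomised women, although ITT is promised for secondary outcomes.

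At stake is the reading of two secondary results, chiefly embryo quality.

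**Working it through.** **1. The plan's own figure (Section 2.9.1).** Inputs: difference 1 oocyte, SD 3, two-sided alpha 5%, power 90%, dropout 20%.

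- Normal approximation: n = 2 × (1.96 + 1.2816)² × 3² / 1² = 189.1, so 190 per group; 190 / 0.80 = 237.5, so 238 per group and 476 in total.
- t-test version: 191 per group; 191 / 0.80 = 238.75, so 239 per group and 478 in total.

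The stated 480 is reproduced within rounding. It concerns one oocyte count per woman, so embryo clustering does not touch it. The article states no figure for the per-embryo outcomes.

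**2. Formulas for the per-embryo outcomes.** With m embryos per woman and intraclass correlation ICC:

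- Design effect: DE = 1 + (m − 1) × ICC. When m varies between women, replace m by E[m²] / E[m].
- True type I error of the unadjusted test: 2 × (1 − Φ(1.96 / √DE)).
- Correct interval width = unadjusted width × √DE.

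**3. Assumed inputs.** The article gives neither an ICC nor an embryo count, so all of these are assumptions:

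- ICC 0.05 to 0.5.
- 192 women per arm (240 × 0.80).
- Good-quality embryos: oocytes with mean 4 and SD 3, each giving an embryo with probability 0.6, so a mean of 2.4 embryos per woman; rate 40%.
- Implantation: 0, 1 or 2 embryos transferred with probabilities 0.3, 0.3 and 0.4; rate 15%.

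**4. Effective cluster sizes.**

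- Good-quality embryos: variance of m = 0.6² × 9 + 0.6 × 0.4 × 4 = 4.2; E[m²] / E[m] = (4.2 + 2.4²) / 2.4 = 4.15.
- Implantation: E[m] = 0.3 + 0.8 = 1.1; E[m²] = 0.3 + 1.6 = 1.9; ratio 1.73.

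**5. Results.** Type I error at nominal 0.05, by formula and by beta-binomial simulation (8,000 runs per setting):

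| ICC | Good-quality embryos: DE | formula | simulated | Implantation: DE | formula | simulated |
|---|---|---|---|---|---|---|
| 0.05 | 1.16 | 0.069 | 0.072 | 1.04 | 0.054 | 0.053 |
| 0.1 | 1.32 | 0.087 | 0.084 | 1.07 | 0.058 | 0.063 |
| 0.2 | 1.63 | 0.125 | 0.129 | 1.15 | 0.067 | 0.068 |
| 0.3 | 1.95 | 0.160 | 0.155 | 1.22 | 0.076 | 0.071 |
| 0.5 | 2.58 | 0.222 | 0.233 | 1.36 | 0.093 | 0.087 |

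When the same simulated data were tested with a between-woman variance, type I error was 0.046 to 0.055 throughout.

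**6. Why variable cluster size matters.** A fixed m of 2.9 (about the simulated mean among women with any embryo) gives DE = 1 + 1.9 × 0.2 = 1.38 and type I error 0.095 at ICC 0.2, against 0.129 simulated. Women with many embryos dominate the pooled rate, so the equal-size formula understates the problem for embryo quality.

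**The case against.** - **The chi-square is not tied to these outcomes by name.** This is true. Section 2.9.2 gives one list for everything, and the chi-square is inferred as the listed test that fits a frequency outcome. One could instead compute a rate for each woman and compare the groups by Wilcoxon or t-test, which would remove the clustering. That reading does not match outcomes defined per embryo, one of them as sacs over embryos transferred.

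- **Methods for secondary outcomes belong in an analysis plan that is not shown.** Silence would not be a finding. Here the article states both the unit and the tests, and followed as written they give an invalid comparison.

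- **Poor responders have few embryos, so clustering is trivial.** This largely stands for implantation: two is a maximum per transfer, and repeated transfers are mentioned only for cumulative live birth. A reader might take every woman to contribute exactly two embryos, which gives 7.4% at ICC 0.2 and 9.8% at ICC 0.4, but the article does not support that. With 0 to 2 embryos, even ICC 0.5 gives only about 9%. The objection fails for embryo quality, where an assumed mean of 2.4 embryos already gives 7% at ICC 0.05.

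- **The denominator problem is a different issue.** This is correct, and a GEE does not cure it. The article also already has outcomes over all randomised women: clinical pregnancy and early miscarriage. What remains is how the per-embryo rates are described.

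A reader might also infer that the pilot's one positive finding was in this same rate and will be promoted. The Discussion says only that high-quality embryos were more after EZTG. It does not say that the difference was in the per-embryo rate, and any later emphasis is speculation.

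**Conclusion.** The point holds for two secondary outcomes. As written, the plan pairs a clustered unit with tests that assume independence. The direction of the error needs only a positive within-woman correlation, which is to be expected. Its size depends on assumptions: over ICC 0.05 to 0.5, true type I error is about 7 to 23% for good-quality embryos and about 5 to 9% for implantation. That is a clear problem for the first and a modest one for the second; it would be larger for implantation if frozen transfers were counted.

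A reader might go further and conclude that the trial's main result or its size is unsound. The documents do not support that, because the primary outcome is one count per woman and the sample size is reproduced. Nor do they show that a chi-square test on pooled embryos has been expressly chosen for these rates. What they show is that no listed test suits a per-embryo unit.

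**What to change.** In Section 2.9.2, state that the good-quality-embryo rate and the implantation rate will be compared by a logistic GEE, or a logistic model with cluster-robust variance, with the woman as the cluster. State also whether the implantation rate counts frozen as well as fresh transfers.

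Separately, describe both rates as conditional on having embryos or a transfer. Report the number of good-quality embryos per randomised woman, with 0 if none, as a supportive ITT comparison.

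The cost is a change of analysis wording; no further participants or data are needed. Intervals widen by the square root of the design effect: √1.4 = 1.18 and √1.8 = 1.34, so 18 to 34% wider at design effects of 1.4 to 1.8. Where clustering is material, that widening is not negligible.
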